#### Diagnostic interview

2.3.3

To validate *the app* against a clinical gold-standard for diagnosing DSM-5 [26] and ICD-11 [27] substance-related disorders; a diagnostic interview will also be conducted with each participant, on the same day as they complete the ASSIST app. The interview is based on the DIS-SAM [28], which has been modified to identify the presence or absence of clinical symptoms for ICD-11 (for hazardous use, harmful use, and dependence) and DSM-5-TR substance use disorder, and includes assessments at both the past 12-month, and past 3-month intervals.

The interview will be conducted by either a male or female health professional (matched to participant's gender). The health professional will understand Pitjantjatjara culture and context but may not be Aboriginal or fluent in the language. Therefore, in addition, an Aboriginal man or woman will also be present at all times to aid interpretation of questions. The choice to include both Aboriginal and non-Indigenous Australian healthcare workers was taken to mitigate the risk that the differences in culture will impact the quality of the assessment [20,21,29]. Interviewers assessments will be based on use in the past 90, and 365 days.

The interview will follow a semi-structured *yarning*-style approach based on a clinical yarning framework. Clinical yarning is a culturally secure framework for clinician-client communication with Aboriginal and/or Torres Strait Islander peoples [30]. This approach has been developed specifically to address the well-documented communication barriers that exist between Aboriginal and Torres Strait Islander peoples and mainstream healthcare services, which often result in misdiagnosis, under-diagnosis, and poor therapeutic engagement [31]. To ensure comprehensive assessment of DSM-5-TR and ICD-11 substance use disorder criteria while maintaining cultural appropriateness, the interview contains a clinical checklist that maps yarning conversation topics to specific DSM-5-TR and ICD-11 criteria. Interviewers will be encouraged to use their discretion to introduce culturally appropriate metaphors, examples, or explanations to support participant understanding and comfort, while still ensuring that all required clinical content is covered. The clinical yarning framework has been shown to reduce communication barriers, and promote greater levels of trust and engagement, while maintaining diagnostic rigour [[31], [32], [33]]; and has been successfully implemented in similar contexts [34]. Where possible, interviews will be kept to 30 minutes or less to minimise participant burden.

#### Independent clinical evaluation

2.3.4

Participants recruited from the DASSA withdrawal service will also undergo an independent clinical evaluation from an addiction medicine specialist, trained to diagnose the presence or absence of ICD-11 and DSM-5-TR disorders related to substance use. The registrar will be blinded from the outcome of the earlier assessment and will provide a clinical opinion as to whether the individual in their care meets the diagnostic threshold for hazardous use, harmful use or dependence (ICD-11) and substance use disorder (DSM-5-TR) for each of the five substances. In all cases, the individual will be known to the clinician (as a patient of the service).

### Data and protocol monitoring

2.4

A data monitoring team — comprised of the first and last author — will work closely with investigators to monitor trial conduct and safety, assess risks and benefits, and make recommendations to protect the participants of clinical trials. To ensure adherence to study protocols, a small group of three-to-five research assistants will be trained extensively to conduct the assessments and interviews. A copy of the study protocol will be provided to each research assistant, interviewer, and interpreter. A regular monthly check in with the group is scheduled to discuss any issues with data collection and study protocol. Any protocol deviations will be reported in writing to each ethics committee within 72 h. No steering committee or other oversight groups are involved beyond the data monitoring team. Trial conduct will be audited monthly by the data monitoring team to ensure protocol adherence.

## Statistical approach

3

A detailed statistical analysis plan is available as an appendix (see supplementary materials). Once all data has been collected, a cleaned, de-identified dataset will be stored within an online repository [35]. The primary outcomes from this study include *the app*'s reliability, validity, diagnostic accuracy, and cultural acceptability. Reliability will be assessed according to internal consistency and test-retest. Validity will be assessed according to both concurrent and discriminative validity against a gold-standard clinical interview outcomes and symptom counts. A small subset of participants will also receive an independent evaluation from a Specialist Addiction Medicine Registrar, which will form the basis of an additional check for concurrent validity. Diagnostic accuracy of the instrument will be assessed based on a range of indices and receiver operating characteristics (ROC) curve analysis. Finally, *the app* will also be assessed for its overall cultural acceptability. As part of initial data screening, count distributions, dispersion characteristics, and relevant modelling assumptions will be examined. *Note*: if any of the following assessments indicate substantial deviation from planned analytic assumptions (e.g. zero-excess, or non-linearity), appropriate modifications to the analysis strategy will be implemented and fully described in the final analysis report.

### Reliability

3.1

#### Internal consistency reliability

3.1.1

Internal consistency reliability will be assessed for each of the five substances using McDonald's Hierarchical Omega (ω_*h*_). Hierarchical Omega estimates the reliability of a general factor in potentially multidimensional scales [36,37] which is expected to be the case in this analysis. Additional coefficients (Total Omega [ω_*T*_] and Cronbach's Alpha [α]) will also be calculated and reported for completeness. Importantly, since SSIs contain a small number of items (five for tobacco, or six for the remaining substances), bootstrapping will be used to approximate the distribution of the all coefficients within a given range, using *n* = 10,000 samples to accommodate biases related to too few scale items [38]. This will calculate a distribution of values for each coefficient, which we could reasonably expect from our sample. A significant (two-tailed *p* < 0.05) ω_*h*_ coefficient ≥0.7 will indicate acceptable internal consistency reliability.

#### Test-retest reliability

3.1.2

Test-retest reliability will be assessed by asking participants to complete the app twice within a period of between 7 and 28 days. Reliability will be indicated through Intraclass Correlation Coefficients (ICC_3,1_ [two-way, mixed-effects, absolute agreement, single rater]) at the scale level. ICC values for each item will also be calculated and reported for completeness. Significant (two-tailed *p* < 0.05) ICC ≥0.5 will indicate acceptable agreement [39,40].

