**Methods:**

Recruitment will occur at a variety of Aboriginal health and welfare settings across remote, rural and urban South Australia. Eligible participants (aged 18–65) will be briefed and, upon consent, randomly complete the ASSIST app on an iPad and a semi-structured, yarning-style diagnostic interview (see endnote 1) with a health professional and Pitjantjatjara interpreter. The interview will assess for a range of clinically-defined substance use disorders (based on DSM-5-TR and ICD-11 criteria). All participants will be asked to complete the app a second time (between 7 and 28 days) to assess reliability, while a subset of participants at highest-risk will also undergo specialist evaluation from an independent clinician, as a second check for validity.

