Participants randomised to the interview-first condition will sit down with the independent researcher/interpreter to conduct the yarning-style interview. At the outset, participants will be asked the same four initial anonymous identifier questions for the purposes of matching data from the interview and app. All interviews will be conducted face-to-face. All data will be recoded in REDCap. Participants will receive $30 voucher for completing the interview. Participants will then be given a short break before completing *the app*.

Upon completion, a follow-up appointment will be scheduled with participants for within fourteen days. At follow-up participants will also be asked to complete *the app* assessment component again (i.e., but not the interview), in order to assess *the app*'s test-retest reliability. To maximise follow-up retention, participants will receive a final $30 voucher, but only upon completion of the final assessment.

For participants taking part in the DASSA withdrawal service (i.e., those representing a higher risk group), an independent clinical assessment, conducted by an Addiction Medicine Registrar employed at the service, will also be used as an additional check of validity. The independent assessment form will include the same unique participant code (see preceding *2.3.1. Unique participant code* section), as well as participants’ age and gender. The assessment will be recorded on a digital form in REDCap and will be completed by the doctor at the service.

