### Sample Size and Power Calculations

**3.5**

For the validity assessments, a series of power calculations were conducted to determine the minimum sample size needed to detect a large between-groups effect, with type-I, and type-II error rates of 5 % (corresponding to α = 0.05), and 10 % (corresponding to an *a priori* power of 90 %) respectively. Where possible, we will also aim to recruit a 1:1 ratio of participants for each group (i.e., positive/negative cases), and so a 1:1 ratio of participants was used here. Using these parameters as default, we conducted the following power calculations in G-power [43].

For each regression model assessing concurrent validity, it was determined that a minimum of 111 participants are needed for each model (corresponding to line-of-best-fit slope of 0.3). For each logistic regression model assessing concurrent validity with the independent assessment, a total sample size of 62 using each substance was determined. The additional parameters used in this analysis included a probability of reaching diagnosis in the diagnosis present group of 0.70 (corresponding to a sensitivity of 70 % and an Odds Ratio of 2.33 [0.70/0.30]), versus a chance probability (i.e., 50%) in the diagnosis absent group. These parameters yielded a total sample size of 62 individuals (approximately 31 in each group diagnosis present/absent assuming 1:1 sampling). For each ANOVA model assessing discriminant validity, a minimum of 96 participants using each substance are required to power the analysis (corresponding to *η*^2^ = 0.14 [44]). Based on this, the minimum number of participants to detect a large effect (Cohens’ *d* > 0.80 [45]) was 38 participants for each group. This corresponds to thirty-eight low risk, thirty-eight moderate risk, and thirty-eight high-risk individuals for each substance (which equals approximately 114 participants for each given substance). For the reliability assessment, we also calculated the minimum sample size required to detect reliability coefficients >0.70, setting the type-I error rate to 0.05, with a minimum power of 0.90, with the number of scale items equal to 4 (tobacco) or 5 (all other substances). This method has been suggested previously [46] and has been used widely in health and medical research settings [47]. The result was a minimum sample size of 38 for a 5-item scale, and 40 for the 4-item scale. We elected to use 40 as the minimum sample size required for consistency.

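### The retest is booked within 14 days with no lower bound, but test-retest reliability is defined on 7 to 28 days; the ICC label and one item count also need correcting

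*Protocol article*

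**What the plan says.** **Retest window.** Section 3.1.2 states: "Test-retest reliability will be assessed by asking participants to complete the app twice within a period of between 7 and 28 days". The abstract matches it: "All participants will be asked to complete the app a second time (between 7 and 28 days) to assess reliability". The Procedure section (2.2.4), which tells staff what to arrange after the first session, says instead that "a follow-up appointment will be scheduled with participants for within fourteen days".

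**Coefficient.** Section 3.1.2 specifies "ICC_3,1_ [two-way, mixed-effects, absolute agreement, single rater]) at the scale level". Its criterion is "Significant (two-tailed *p* < 0.05) ICC ≥0.5 will indicate acceptable agreement".

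**Item counts.** Section 3.1.1 on internal consistency says "SSIs contain a small number of items (five for tobacco, or six for the remaining substances". Section 3.5 calculates the reliability sample size "with the number of scale items equal to 4 (tobacco) or 5 (all other substances", and arrives at 38 for a 5-item scale and 40 for a 4-item scale, of which 40 is adopted.

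Section 3 lists reliability among the primary outcomes and names test-retest as one of its two components.

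**The concern.** Staff book appointments from the procedure. Section 2.4 gives every research assistant, interviewer and interpreter a copy of the protocol, has adherence audited monthly, and requires deviations to be reported to each ethics committee within 72 hours. With two windows in the text, a retest on day 5 or day 20 both complies and deviates, depending on the section consulted.

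The interval also bears on the estimate. A retest after a few days may raise agreement through recall. Once a retest has been done its interval cannot be altered, so a separate analysis plan cannot repair this afterwards.

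The ICC label matters because the consistency form ignores a systematic shift between occasions and the absolute-agreement form penalises it. A shift is conceivable here: the app shows users their calculated risk (section 2.3.2), and they have a diagnostic interview on the same day (section 2.3.3), both before the retest.

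**Working it through.** **1. The window.** Counting days from the first app session, with day 1 as the earliest retest:

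| Retest day | Procedure, 2.2.4 (within 14 days) | Abstract and 3.1.2 (7 to 28 days) |
|---|---|---|
| 1 to 6 | inside | outside |
| 7 to 14 | inside | inside |
| 15 to 28 | outside | inside |

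The procedure allows 14 days, of which 6 lie outside the reliability window. The reliability window covers 28 − 7 + 1 = 22 days, of which 14 lie outside the procedure. Both rules hold on 8 days.

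**2. The ICC form.** Let T be between-person variance, E error variance, T + E = 1, and let d be the mean shift between the two occasions in SD units.

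- Consistency = T / (T + E)
- Absolute agreement = T / (T + E + d²/2)

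The documents give no value for T or d, so these are assumptions. With T = 0.70 and E = 0.30, consistency is 0.70 throughout:

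- d = 0.5: 0.70 / (1 + 0.125) = 0.62, which passes 0.5 under both forms.
- d = 1: 0.70 / (1 + 0.5) = 0.47, which passes under consistency and fails under absolute agreement.
- The forms part at 0.70 / (1 + d²/2) = 0.5, so d² = 0.8 and d = 0.89.

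Nearer the criterion a smaller shift is enough. With T = 0.55, d² = 0.2 and d = 0.45. In 2,000 simulated samples of 40 with true consistency 0.55:

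| Shift (SD) | Mean consistency | Mean absolute agreement | Estimate ≥ 0.5, consistency | Estimate ≥ 0.5, agreement |
|---|---|---|---|---|
| 0 | 0.54 | 0.54 | 66% | 67% |
| 0.5 | 0.54 | 0.49 | 68% | 47% |
| 1.0 | 0.54 | 0.37 | 68% | 7% |

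These percentages concern the point estimate only, not the accompanying significance test.

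**3. The item count.** Inputs from section 3.5 are a target coefficient of 0.70, α = 0.05 and power 0.90. The null value r₀ and the sidedness are not given there and are assumed. The usual formula for testing coefficient alpha with k items is

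n = [2k/(k − 1)] × (z_α + z_β)² / {ln[(1 − r₀)/(1 − 0.70)]}² + 2

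Two-sided, (1.960 + 1.2816)² = 10.51. With r₀ = 0.30, ln(0.70/0.30) = 0.847, whose square is 0.718.

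| Assumption | k = 4 | k = 5 | k = 6 |
|---|---|---|---|
| r₀ = 0.30, two-sided | 41.03 | 38.59 | 37.13 |
| r₀ = 0.35, one-sided | 40.20 | 37.81 | 36.38 |
| r₀ = 0, two-sided | 21.33 | 20.12 | 19.40 |

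The plan's 40 and 38 are therefore plausible but cannot be confirmed from the stated inputs. A two-sided null of 0.287 reproduces both after rounding up, and gives 36 for six items. With 5 and 6 items the requirement becomes 38 and 36 under that null, or 39 and 38 under r₀ = 0.30 two-sided. All are below 40.

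**The case against.** **On the window.** Two of the three places agree, and the third describes when an appointment is made. A 14-day booking target inside a wider acceptance window is a sensible reading, under which rebooked or late retests would fall on days 15 to 28. That stands in part: a reader might infer that those days would go unused, or that early retests would be dropped, but the text establishes neither, since it has no rule excluding out-of-window retests. The objection does not remove the conflict. The text does not say that 14 days is a target, and on that reading too the procedure permits days 1 to 6.

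**On the ICC.** The bracket spells the coefficient out as "two-way, mixed-effects, absolute agreement, single rater", and the criterion speaks of agreement. The intended form is therefore readable and only the subscript is out of line with common notation. This stands. A change of pass or fail needs either a shift near 1 SD or a true value close to 0.5, and the documents suggest neither. A reader might infer that the test-retest result is undefined; the written definition does not support that.

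**On the item counts.** A reader might count this mismatch against test-retest as well. It does not belong there. The item count enters only the sample size for a coefficient above 0.70, the level set for omega in section 3.1.1. The ICC has its own criterion of 0.5 and uses no item count. It is also fair to say that the items 2 to 7 described in section 2.3.2 support six items but do not by themselves establish five for tobacco; that figure rests on section 3.1.1.

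**Conclusion.** The window contradiction holds and is the point that needs action. For part of a primary outcome, the procedure and the analysis definition agree on days 7 to 14 only, and the procedure admits retests on days 1 to 6 that the reliability definition excludes. This rests on the text alone. Its effect on the ICC cannot be sized, because the documents give no distribution of retest days and no rate of change in scores.

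The ICC point is a mislabel. Its possible effect (0.70 becoming 0.62 or 0.47) depends on assumed shifts of 0.5 and 1 SD and on an analyst following the label over the definition.

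The item-count conflict is a minor error in the internal-consistency sample size. Correcting it lowers n by about two, and the adopted 40 remains enough under nulls that approximately reproduce the stated figures.

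**What to change.** 1. **Window, before retests are booked.** Reconcile the abstract, section 2.2.4 and section 3.1.2 to a single window with an explicit lower and upper bound. If 14 days is meant as a booking target inside a wider window, say so. State how retests outside the window enter the ICC. Which window to adopt is for the investigators.
2. **ICC label.** In section 3.1.2 keep the written absolute-agreement definition and replace the (3,1) label, for example with ICC(A,1). Set the software option to match.
3. **Item count.** In section 3.5 restate the internal-consistency sample size with 5 and 6 items, in line with section 3.1.1. The minimum of 40 need not change.

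The cost is a few words in each of these sections, one software setting and one repeated calculation. No extra participants or visits are needed.

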### Validity

3.2

#### Concurrent validity

3.2.1

Concurrent validity will be assessed in two ways. First, a confirmatory approach will assess the partial-order (Spearman's Rho [ρ]) correlation between ASSIST SSI scores for each scale, and the total number of DSM-5-TR and ICD-11 diagnostic symptoms reported for that substance. The use of partial correlations will help to control for the effects of other substances and demographic factors. Benjamini-Hochberg (BH) correction will be used for each correlation to control the False Discovery Rate (FDR) [41]. BH-corrected significant (FDR <0.05) partial correlation ρ ≥ 0.5 will indicate concurrent validity.

The second (exploratory) approach will involve assessing the relationship between ASSIST SSI scores and the number of DSM-5-TR/ICD-11 symptoms through linear and quadratic regression models. For every substance, a regression plot will map the number of ICD-11/DSM-5-TR symptoms reported (vertically along the y-axis) as a function of the ASSIST SSI score (horizontally on the x-axis). As there are five substances, and two distinct classification systems, a total of 20 separate regression models will be carried out (10 linear, and 10 quadratic). For each substance, a significant linear and/or quadratic relationship (*p* < 0.05) is expected to be found between the number of symptoms reported and the average ASSIST scores. Model fit indices will be reported, and models will be compared using AIC and BIC values, to prevent overfitting. Models with the lowest AIC/BIC values will be selected.

A final check for concurrent validity (depending on sufficient data) will investigate the relationship between ASSIST SSI scores for each substance, and the outcomes from the independent clinical assessment by an Addiction Medicine Specialist. For each substance, a logistic regression model will be used to assess the probability of reaching a diagnosis, per unit score increase on the ASSIST. For each substance, a significant model (*p* < 0.05) is expected to be found between the ASSIST scores and the diagnosis probability.

#### Discriminant validity

3.2.2

Discriminant validity assesses the extent to which an instrument can differentiate between two (or more) theoretically independent groups. In this study, groupings will be determined by ICD-11 and DSM-5-TR diagnostic categories respectively. Differences between scores as a function of diagnostic classification will be assessed using initial one-way ANOVA, with a series of planned pairwise t-tests to confirm group-level differences. Ten separate ANOVA models will assess whether differences exist in the distribution of ASSIST scores between groups for each substance and classification system (i.e., 5-substances x 2-systems). Table 1 below outlines the planned analysis for the two tests.

**Table 1 tbl1:** One-way ANOVA models assessing group differences for ICD-11 (Model set 1) and DSM-5-TR (Model set 2).

Model set	Diagnostic Severity Group (per substance)			
1	No disorder	Hazardous use	Harmful use	Dependence
2	No SUD	Mild SUD	Moderate SUD	Severe SUD

In the first set of models, score distributions will be compared based on ICD-11 diagnostic classifications for each substance, while the second set of models will compare score distributions based on DSM-5-TR diagnostic classifications. If a significant omnibus test is found (i.e., *p* < 0.05) for each substance/classification, as expected, three planned (*a priori*) pairwise comparisons using BH-correction (setting FDR <0.05) will assess the magnitude and direction of those score differences.

Table 2 below outlines the planned comparisons to be carried out. For each substance, the first set of planned comparisons will assess the ability of the Pitjantjatjara ASSIST SSI to discriminate between the absence of DSM-5-TR or ICD-11 disorder, versus mild SUD and hazardous use, respectively. The second set of comparisons will assess the ability of the SSI to discriminate between mild vs moderate SUD; or between hazardous vs harmful use, respectively. The third set of comparisons will assess the ability of the SSI to assess risk between moderate vs severe SUD; and between harmful use vs dependence, respectively (see Table 2).

**Table 2 tbl2:** Planned (A vs. B) pairwise comparisons of ASSIST scores by ICD-11/DSM-5-TR diagnoses.

Planned comparisons		No disorder/No SUD	Hazardous use/Mild SUD	Harmful use/Moderate SUD	Dependence/Severe SUD
1	Low risk	A	B	*excluded*	*excluded*
2	Mod. risk	*excluded*	A	B	*excluded*
3	High risk	*excluded*	*excluded*	A	B

